### Strategies for subject retention

We selected survey instruments to minimize respondent burden. In preliminary testing, respondents completed the battery of tests in less than 15 minutes. At baseline the research assistant administer the questionnaire with the use of visual aids to help with answering the questions. When obtaining the consent, patients will be informed of the follow up survey and the same research assistant will contact the patients at six months. This will help in establishing a rapport and increasing the response rate at follow-up. The average retention rate for the surveys conducted by the QOL research team at our institution is in excess of 80%.

### Quality control and data management

LIPS study collects a large number of data regarding patient exposures and outcomes. To reduce measurement error, a comprehensive data quality assurance program will be employed. Data will be maintained on a secure server with nightly back up. Single Mayo logon LAN ID (local area network identification) provides access to the data to authorized individuals. Electronic range checks and validation rules will eliminate erroneous data entry and artifacts in numeric values. As an independent quality control measure periodic audits of the database will be performed. Routine descriptive statistics will be obtained at regular intervals to assure completeness of data collection.

### Statistical Analysis

An estimate for the probability of ALI development will be calculated for each patient based on the LIPS model. Because of subjective nature of clinical definitions used to identify the outcome of our study, it is necessary to assess interobserver variability. Interobserver agreement for ALI development will be assessed by calculating the Kappa statistic, using a threshold of 0.6 as an indication of acceptable interobserver agreement.

The calibration and discrimination of model will be assessed using the Hosmer-Lemeshow goodness-of-fit test and the receiver operating characteristic curve, respectively. An area under the ROC curve greater than 80% will be considered to be the evidence of good model discrimination. Using a LIPS cutpoint of 3.5 or more identified in the preliminary data, the comparison of the model prediction versus the actual event observed will be summarized by a simple 2 by 2 table reporting ALI propensity versus ALI development. Summary measures, based on the 2 by 2 table, will be reported: sensitivity, specificity, positive predictive value, negative predictive value, positive and negative likelihood ratios along with their 95% confidence intervals.

In a matched case-control design the associations suggested by preliminary clinical studies (Table 3) will be compared between ALI cases and high risk controls propensity matched by age, gender and the probability of ALI development at the time of hospital admission (LIPS, see above). Subpopulation analyses will be performed to determine what hospital exposures are associated with ALI in low/moderate ALI risk patients and what hospital exposures factors are associated with no ALI development in high ALI risk patients. The primary statistical endpoint is the development of ALI at any time during hospital stay. The matching is based on ALI risk at admission and the exposure period at risk. For example, if a hospitalized patient, who has an estimated propensity for developing ALI of 20% actually develops ALI 10 hours after hospital admission the exposures in matched control patient is only measured during the initial 10 hours after hospital admission. Paired statistics will be used for group comparisons. A conditional logistic regression model will be built in the case of baseline imbalances.

The statistical endpoints for determining attributable burden of ALI development in patients at risk are unadjusted and quality adjusted survival after hospital admission. All patients will be followed until death or study conclusion, and patients who survive will be censored at the last date known to be alive. In addition, we will assess which hospital exposures, impact the long-term survival and quality-adjusted survival in both ALI patients and high risk controls. We will use Kaplan-Mayer survival curves to depict survival differences in these subgroups. In order to understand the impact of ALI on quality of life, we will compare the l quality of life measures between the ALI patients and controls, taking into account the correlations between serial (baseline and follow up) QOL measurements. We will carry out quality-adjusted life years (QALY) analyses to incorporate the QOL-related health state utility variables into the survival analysis. We will combine survival and quality of life using the time spent in specific "health state" (ventilator, ICU, hospital, nursing home, home) to describe the quality adjusted survival of ALI patients according to the following formula:

We expect that missing data will be minimized due to the error checking capability of our data entry system. We will handle missing data in a number of ways including complete case analysis and imputation via nearest neighbor, mean value, last value, and zero value carried forward approaches. Multiple approaches are used so that the sensitivity of results to alteration in imputational assumptions may be assessed.

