### Early identification of patients at risk of ALI (lung injury prediction score - LIPS)

To facilitate enrollment of patients into mechanistic and outcome studies as well as future ALI prevention trials, we have recently developed an ALI prediction model (Lung Injury Prediction Score: LIPS, Table 1)[22]. LIPS incorporates demographic, and clinical characteristics at the time of, and before, hospital admission. Risk factors for ALI that were identified in at least two previous studies were used in model development. LIPS points were determined based on parameter estimates from the logistic regression model, taking into consideration results from our previous studies. The model accurately discriminated between the patients who did and did not develop ALI with an area under the receiver operating curve of 0.85 (95% CI 0.80 to 0.89) [22].

Twice daily (7 AM and 5 PM, Monday-Saturday) trained study coordinators review syndrome surveillance alerts of new Olmsted County admissions and apply LIPS points to patients who fulfill the inclusion criteria according to LIPS score sheet. ODBC MS Access database tool is used for the collection of individual patient data in a systematic way. The database automatically links MS Access to ICU Datamart server and imports new patients from ICU Datamart to the LIPS database. The database also links automatically to the IRB research authorization web site identifying the patients that have approved the use of their medical data for research.

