### Sample size considerations

Planned enrollment of 500 ALI cases guarantee an adequate sample size for LIPS validation. If we have 500 ALI cases and 80% score above the threshold for the ALI model (sensitivity) then our precision will be .02 and the 95% CI would 0.78 to 0.82.

A comparison of 500 ALI cases with 500 propensity matched high risk controls will allow us to determine moderately high associations (odds ratio >2.0) between common in-hospital exposures (prevalence >5%, i.e. variability in fluid management, transfusion, antibiotics, FIO2, mechanical ventilation) and ALI development (Figure 3). We will be able to identify only strong associations for less common in-hospital exposures (<5%).

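### LIPS calibration is assessed only by the Hosmer-Lemeshow test, which reports neither the size nor the direction of miscalibration; add calibration estimates with confidence intervals and a plot

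*Protocol article*

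**What the plan says.** In the protocol article, Statistical Analysis, calibration and discrimination are each given one tool: "The calibration and discrimination of model will be assessed using the Hosmer-Lemeshow goodness-of-fit test and the receiver operating characteristic curve, respectively". Discrimination has a numerical benchmark: "An area under the ROC curve greater than 80% will be considered to be the evidence of good model discrimination". Calibration has none, and the number of groups, the degrees of freedom and the significance level are not given. The other comparison of prediction with outcome is at the LIPS cutpoint of 3.5, "summarized by a simple 2 by 2 table reporting ALI propensity versus ALI development", with 95% confidence intervals for sensitivity, specificity, predictive values and likelihood ratios. That measures classification at one threshold, not whether the predicted probabilities are right.

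The probabilities themselves are used. The same section states: "An estimate for the probability of ALI development will be calculated for each patient based on the LIPS model". Controls are "propensity matched by age, gender and the probability of ALI development at the time of hospital admission". The LIPS section says the score comes from earlier work: "LIPS points were determined based on parameter estimates from the logistic regression model".

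Sample size considerations presents validation as an aim: "Planned enrollment of 500 ALI cases guarantee an adequate sample size for LIPS validation". The justification there concerns the precision of sensitivity only. The size of the at-risk cohort that would yield 500 cases is not stated.

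**The concern.** A validation should tell users how far the predicted risks are from the observed risks, and in which direction. The Hosmer-Lemeshow test gives one p-value. A small p-value says that some departure was detected, but not whether it is large enough to matter or whether LIPS predicts too high or too low. A large p-value may mean good calibration or low power for the kind of error present. For a fixed error, the non-random part of the statistic grows in proportion to the number of patients, so the verdict also depends on a cohort size that the article leaves open.

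At stake is the usefulness of the validation. The LIPS section says the score is meant to support enrolment into future prevention trials. There, a systematic over- or underprediction of absolute risk feeds directly into expected event counts.

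**Working it through.** The article gives no figure for calibration, so there is none to reproduce. The check is a simulation of the named test.

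**Inputs from the article:** 500 ALI cases (Sample size considerations); area under the curve 0.85 (LIPS section).

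**Assumptions, not in the article:** ALI incidence of 5%, 10% or 20%, so that 500 cases imply 500/0.05 = 10,000, 500/0.10 = 5,000 or 500/0.20 = 2,500 patients; ten risk groups; a normally distributed linear predictor; a 5% test level.

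**Statistic:** HL = sum over groups of (O - E)² / [E(1 - E/n)], with O and E the observed and expected events and n the patients in a group. It is referred to chi-square with 10 degrees of freedom (the number of groups, g, for a model fixed in advance) or 8 (g - 2, for a model fitted to the same data).

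**Step 1: same error, different cohort size.** Incidence 10%, linear predictor tuned to an area under the curve of 0.85, 10 degrees of freedom, 800 runs. O/E is the observed/expected ratio.

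| Error | N=1,000 | N=5,000 | N=10,000 | N=20,000 |
|---|---|---|---|---|
| O/E 0.90 (mean error 1.0 point) | 5.5% | 30% | 69% | 96% |
| Slope 0.9, mean risk correct (0.7 points) | 17% | 35% | 67% | 92% |

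The error is identical along each row, yet the verdict moves from usually passing to almost always failing.

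**Step 2: same cohort size, different error.** At N=5,000 in the same set-up, rejection is 6% with no error, 30% at O/E 0.90 and 100% at O/E 0.75. It is 35% at slope 0.9 and 97% at slope 0.8. The test does respond to magnitude; the p-value does not separate magnitude from sample size.

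**Step 3: similar mean error, different kind.** About 500 events, linear predictor SD 1.6, 10 degrees of freedom. Ranges cover repeated runs of 500 to 2,000 cohorts; single values are from 2,000.

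| Incidence, N | Slope 0.9, mean risk correct | True odds 10% below predicted | True odds 11% above predicted |
|---|---|---|---|
| 5%, 10,000 (mean error about 0.4 points) | 43-46% | 12-16% | 26-28% |
| 10%, 5,000 (about 0.7-0.8 points) | 35-39% | 15% | 27% |
| 20%, 2,500 (about 1.1-1.3 points) | 25-32% | 13% | 20% |

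In the first row, odds 10% below predicted give O/E of about 0.92, so predicted exceeds observed by 1/0.92 - 1 = 8.7%. That systematic overprediction is missed in 84-88% of cohorts, while the model with correct mean risk is rejected nearly half the time. At 10% and 20% incidence the same shift in odds gives O/E of 0.93 and 0.94, an overprediction of about 8% and 6%.

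**Step 4: what a direct estimate would show.** With 500 expected and 0.92 × 500 = 460 observed events, O/E is 0.92. Taking the variance of the observed count as at most 460 (Poisson), the 95% half-width is 1.96 × √460 / 500 = 1.96 × 21.4 / 500 = 0.084, so the interval is about 0.84 to 1.00. The reader sees the direction and learns that overprediction of up to 1/0.84 - 1 = 19% is compatible with the data. A non-significant test conveys neither.

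**Step 5: degrees of freedom.** For a perfectly calibrated fixed model with N of 2,500 or more, false rejection is about 10-12% with 8 degrees of freedom and 4-6% with 10.

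**The case against.** The strongest reply is that this is a condensed article, that a plot or slope is not excluded, and that such detail often sits in a fuller plan. That holds for the number of groups and the degrees of freedom. It holds less well for the choice of method: the article names one calibration method as it names one discrimination method, and that choice can be judged as stated.

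Several stronger readings are tempting but unsupported:

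- A reader might infer that the test ignores the size of miscalibration. Step 2 shows that it does not.
- A reader might infer that matching on the LIPS probability carries miscalibration into the case-control comparison. Cases and controls are scored by the same model. An error in intercept or slope keeps patients in the same order, so the pairs stay largely unchanged apart from any caliper. The article also provides conditional logistic regression for baseline imbalance. Bias in that comparison is not shown.
- A reader might infer that the plan uses the wrong degrees of freedom. It states none. Nor does it say how LIPS points become probabilities. If that mapping were fitted in this cohort, g - 2 would be appropriate, and an intercept and slope assessed on the same data would be 0 and 1 by construction.
- A reader might infer that a usable score would be formally discarded. The article sets no pass rule for this test, so the risk lies in interpretation.

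It is also fair that the slope result depends on how the error is defined. A slope of 0.9 that also shifts mean risk (O/E 0.94 to 0.87) is rejected more often, about 40%, 61% and 76% at 20%, 10% and 5% incidence. Rejection there is less clearly a fault, so the working uses the slope error with mean risk held correct.

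**Conclusion.** The point stands as a weakness of the LIPS validation, worth correcting but not threatening the study's main comparison. The only calibration method named cannot say how large the error is or which way it runs, and its verdict for a given error depends on an unstated cohort size. In the clearest illustration (5% incidence, 10,000 patients), an 8-9% overprediction of mean risk is detected about 12-16% of the time, against 43-46% for a model of similar mean error whose average risk is right. These rates rest on the assumed incidences, ten groups, a normal linear predictor and 10 degrees of freedom. At 20% incidence the contrast narrows to about 13% against 25-32%. The qualitative conclusion does not depend on the exact rates.

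**What to change.** Make the calibration assessment consist of calibration-in-the-large (or the observed/expected ratio) and the calibration slope, each with a 95% confidence interval, together with a smoothed plot of observed against predicted risk. Apply these to LIPS probabilities whose mapping from points was fixed before the validation data, and say so. If Hosmer-Lemeshow is kept, label it supplementary, state the number of groups, and use g degrees of freedom if no parameters are fitted in this cohort.

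The cost is two estimates and one figure from data already being collected. Enrolment, outcome ascertainment and matching do not change.

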**Methods/Design:**

In this population-based observational cohort study, the investigators identify patients at high risk of ALI using the prediction model applied within the first six hours of hospital admission. Using a validated system-wide electronic surveillance, Olmsted County patients at risk are followed until ALI, death or hospital discharge. Detailed in-hospital (second hit) exposures and meaningful short and long term outcomes (quality-adjusted survival) are compared between ALI cases and high risk controls matched by age, gender and probability of developing ALI. Time sensitive biospecimens are collected for collaborative research studies. Nested case control comparison of 500 patients who developed ALI with 500 matched controls will provide an adequate power to determine significant differences in common hospital exposures and outcomes between the two groups.

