## Background

Acute lung injury (ALI) and its more severe form Acute respiratory distress syndrome (ARDS) are common and devastating complications after acute illness or injury with high morbidity and mortality, long term decrease in quality of life, and enormous costs related to intensive care and rehabilitation [1]. ALI is an example of a critical care syndrome with limited treatment options once the condition is fully established. Despite improved understanding of the pathophysiology of ALI, the clinical impact has been limited to improvements in supportive treatment [2,3]. Surprisingly little research has been done on the prevention of ALI. Preclinical studies support a "two hit" model of development of ALI whereby different exposures modify the expression of ALI in susceptible host [4]. Preliminary data suggest that ALI is rarely present at the time of hospital admission but develops over a period of hours to days in subsets of patients with predisposing conditions such as pneumonia, sepsis, trauma, shock and corresponding medical and surgical interventions [5-12]. To this extent, ALI may be viewed as potentially preventable hospital complication similar to stress ulcer bleeding, venous thromboembolism or nosocomial infections. Previous clinical studies enrolled patients after ICU admission, often with already established ALI, beyond the window of meaningful mechanistic studies and potential prevention strategies [13-15]. Not surprisingly, many treatments targeting the mechanisms identified in preclinical studies have failed to improve patient outcomes despite compelling preclinical data [16-19]. It is likely that, inadequate and delayed recognition of patients at risk and the subsequent development of the full blown syndrome have obscured the therapeutic window. ALI usually develops during the first hours of ICU admission, and often is the very reason for ICU admission. On the other hand, the majority of patients with predisposing conditions never develop ALI and they may never been admitted to the ICU making the enrollment of unselected patients into ALI prevention studies neither feasible nor efficient [12,10]. A meaningful approach to ALI prevention therefore ought to be based on identifying patients at risk earlier than what is currently done (at the time of hospital admission, rather than ICU admission, Figure 1) [10].

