### Inclusion Criteria

Olmsted County residents more than 18 years of age admitted to the two Mayo Clinic Rochester hospitals with one or more of the ALI predisposing conditions (sepsis, pneumonia, aspiration, pancreatitis, shock, high risk trauma, and high risk surgery). (Table 1) Exclusion criteria are listed in Table 2. Institutional review board has approved the study protocol.

**Table 1 T1:** Predisposing conditions and modifiers available before or within six hours after hospital admission used to calculate the lung injury prediction score (LIPS):[22].

*Risk factors*	Measurement	Definition
Pneumonia	Yes/No	Consensus Conference[24]
Sepsis	Yes/No, severe	SCCM-ACCP definition[25]
Pancreatitis	Yes/No	Practice guidelines in acute pancreatitis[26]
Aspiration (pre-admission)	Yes/No	Inhalation of food or gastric contents[27]
High risk trauma	Lung contusion, smoke inhalation, near-drowning, multiple bone, brain injury	From Derdak [28]
High risk surgery	Aortic vascular, spine, thoracic, acute abdomen, emergency	From Arozullah et al [29,30]
*Risk Modifiers*		
Alcohol use	Yes/No, amount (# of drinks a week)	More than 2 drinks per day or a history of alcohol-related illness or admission[31,32]
Smoking	Never/former/current/# of pack-years	Substance Abuse and Mental Health
Diabetes mellitus*	Yes/No	Diabetes care 2009[33]
Interstitial lung disease	Yes/No	ATS-ERS Consensus classification of IIP[34]
Chemotherapy	Yes/No	Custom, cancer chemotherapeutic drugs during the 6 months prior to hospitalization
Tachypnea (respiratory rate>30),		Based on the worst value during the first 6 hours
High inspired oxygen concentration (FIO2>0.35)		Based on the worst value during the first 6 hours
Hypoalbuminemia		Serum albumin <3.5 g/dL, the absence of measurement considered normal

*Only if sepsis

**Table 2 T2:** Exclusion criteria.

Exclusion Criteria	Justification
Acute lung injury or pulmonary edema already present at the time of hospital admission	Unable to assess for development of outcome of interest
Admitted for comfort or hospice care only	Missing predictor and outcome variables
Denied the use of medical records for research (~5%)	Self explanatory
Patients admitted for cardiac telemetry, coronary care unit, low risk elective surgeries, labor and delivery	Very low risk of outcome of interest
Children	Different risk factors and outcome
Hospital readmission	Complexity of analysis
Hospital transfer	Exposure to health care interventions

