### Validation of the primary outcome (ALI)

Primary outcome is the development of ALI at any time during the hospital stay. Trained investigators review each ARDS sniffer alert (see above) and confirm the presence or absence of ALI according to the standard definition based on the American-European consensus conference [21]. The absence of left atrial hypertension as the principal explanation for pulmonary edema is confirmed by integrated clinical evaluation based on the following:

• Echocardiography (E/E'<15, EF>45)

• Pulmonary artery occlusion pressure (PAOP) ≤ 18 cm H2O

• Central venous pressure (CVP < 15) cm H2O (higher cutoff in pulmonary hypertension)

• History of congestive heart failure/cardiogenic pulmonary edema

• Brain natriuretic peptide (BNP) <250 pg/mL (higher cutoff in renal failure)

• Response to preload reduction: brisk (hours) response to diuretics and/or positive pressure ventilation favors hydrostatic edema

This process yielded good interobserver agreement for differentiation between ALI and hydrostatic edema (Kappa value 0.83 in the most recent retrospective Olmsted county study)[10].

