**Figure 3 F3:**
[figure not shown]
**Power for a matched case control study of 500 ALI patients matched to 500 controls where the risk factor occurs at 10%, 5%, or 1% prevalence in the controls and the false positive rate is 0.05**. As depicted, if 5% of the controls experience delayed fluid resuscitation which increases the risk of ALI by 2 fold, then the study has about 82% power to reject the null hypothesis.

Assuming a median survival of around 2 years in control population and ALI increases the risk of death by about 1.25, then the study has 80% power to reject the null hypothesis of equal survival of controls and ALI patients. A target of 100 ALI survivors and 100 controls assuming a standard deviation of the health related quality of life score among ICU patients of 10 units, the study has 80% power to detect a difference in self reported quality of life of 4.0 units or greater.

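### Survival is timed from admission although ALI status is set later, and nothing stated requires a control to be alive and ALI-free at the case's onset time

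*Protocol article*

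**What the plan says.** Statistical Analysis defines the burden endpoints: "The statistical endpoints for determining attributable burden of ALI development in patients at risk are unadjusted and quality adjusted survival after hospital admission". Kaplan-Meier curves are to show group differences. Time zero is therefore admission.

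ALI status is fixed later. The section on validation of the outcome states: "Primary outcome is the development of ALI at any time during the hospital stay". The Background says ALI "develops over a period of hours to days in subsets of patients with predisposing conditions". Table 2 excludes "Acute lung injury or pulmonary edema already present at the time of hospital admission", so every case has a positive interval from admission to onset.

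The section on attributable burden contrasts patients who develop ALI with those who do not. The Abstract says exposures and outcomes "are compared between ALI cases and high risk controls matched by age, gender and probability of developing ALI", with no mention of time at risk. Statistical Analysis adds the time at risk as a matching factor when it describes the case-control comparison of exposures. Its worked example, a case with onset at 10 hours, says that "the exposures in matched control patient is only measured during the initial 10 hours after hospital admission".

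Sample size considerations assumes a control median survival of about 2 years and that "ALI increases the risk of death by about 1.25", and claims 80% power.

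**The concern.** Group membership is defined by an event that happens after the clock starts. A case has survived to its own onset by construction. A high-risk patient who dies before any ALI has, by definition, not developed ALI and belongs to the comparison group unless a rule removes that patient. This is immortal time in the ALI group, and it pulls the estimated excess mortality toward zero.

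Quality-adjusted survival has the same time zero, so a case's guaranteed time before onset is credited to ALI survival there too. The size of that effect has not been computed.

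The burden of ALI is one of the three results promised in the Conclusion and is meant to set priorities for prevention. The planned effect is small, so there is little room for dilution.

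**Working it through.** **The plan's own figure.** Read the factor 1.25 as a hazard ratio, with two-sided alpha 0.05 (the article states 0.05 for Figure 3 only) and 500 patients per group. Deaths needed for 80% power (Schoenfeld) = 4 × (1.960 + 0.842)² / (ln 1.25)² = 4 × 7.85 / 0.0498 ≈ 631. With a 2-year control median the yearly hazards are ln 2 / 2 = 0.347 and 1.25 × 0.347 = 0.433. At 2.57 years of fixed follow-up, expected deaths are 500 × (1 − e^(−0.892)) + 500 × (1 − e^(−1.115)) ≈ 295 + 336 = 631. The stated 80% is attainable but cannot be confirmed, because the length of follow-up is not given in years.

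**Early deaths under constant hazard.** Expected control deaths by day 2: 500 × (1 − e^(−0.347 × 2/365.25)) ≈ 0.95. By day 5: about 2.4. About 0.2% of controls die in the first 2 days.

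**Effect of early deaths kept as controls.** Simulation of 500 against 500, 1,500 replicates, follow-up 2.575 years, true hazard ratio 1.25 after onset, overall control median 2 years. A share p of controls dies before the matched onset time; no case can. Power is the chance of a significant result in the direction of harm.

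| p (assumed) | Onset, days (assumed) | HR from admission | Power | HR from onset, controls alive then | Power |
|---|---|---|---|---|---|
| 0.2% | 2 | 1.246 | 77.9% | 1.249 | 78.7% |
| 1% | 2 | 1.232 | 75.1% | 1.255 | 79.3% |
| 2% | 2 | 1.204 | 63.1% | 1.246 | 76.9% |
| 3% | 3 | 1.189 | 56.1% | 1.250 | 78.5% |
| 5% | 3 | 1.139 | 36.7% | 1.252 | 77.8% |
| 5% | 5 | 1.139 | 35.7% | 1.250 | 78.7% |
| 10% | 5 | 1.029 | 5.5% | 1.248 | 73.3% |

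**Hand check at 2%.** Ten early control deaths each lower observed minus expected case deaths by about 0.5, a total of 5. The information is about 625/4 = 156. The shift in log hazard ratio is −5/156 = −0.032, so 0.223 − 0.032 = 0.191, a hazard ratio of 1.21 against the simulated 1.204.

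**Second model.** Control survival S(t) = exp(−ln 2 × (t/730)^k), t in days, with assumed median onset between 10 hours and 4 days.

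| k | 30-day control mortality | Controls dead by day 2 | HR from admission |
|---|---|---|---|
| 1 | 2.8% | 0.2% | 1.24–1.25 |
| 0.7 | 7.2% | 1.1% | 1.20–1.24 |
| 0.5 | 13.1% | 3.6% | 1.12–1.21 |
| 0.35 | 20.3% | 8.4% | 0.99–1.12 |

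If controls must be alive and at risk at the index time, the estimate is 1.24–1.26 throughout.

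**The case against.** The strongest reply is that the matching already solves the problem. A patient who died at hour 5 has no 10-hour period to match to a case with onset at hour 10, and the article describes one set of 500 cases and 500 controls used for both exposures and outcomes. On that reading early deaths never become controls and the bias is essentially nil. The reading is reasonable. It is not stated, though: the sentence sits in the exposure analysis, its example only shortens the window in which the control's exposures are measured, and the Abstract's list of matching factors omits time at risk.

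The second reply is that every material figure needs front-loaded deaths, while the plan's only survival input, taken with a constant hazard, gives almost no bias. That stands as a limit on the claim. Exclusion of comfort-care and hospice admissions also removes some early deaths, and onset within hours shrinks the effect. Against this, the cohort is admitted with conditions such as sepsis, shock and high-risk trauma, for which a constant hazard from day 0 is hard to defend.

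Third, survival from admission is a coherent endpoint for patients at risk at admission. That is true, and a time-dependent ALI term would keep it. The article names no such term.

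**Conclusion.** The point holds as a conditional one. The stated time zero precedes group assignment, cases are event-free until onset by construction, and no stated rule for the survival comparison handles this. If early deaths without ALI are kept in the comparison group, the bias is toward no effect. It is negligible under constant hazard with the 2-year median. It is material from about 2% of controls dead before the matched onset time, and at about 10% the effect is nearly gone. The article gives no early-death share, so these figures show sensitivity and do not forecast the result.

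A reader might infer three stronger things that the document does not support:
- That early deaths certainly count as controls. The time-at-risk matching may exclude them.
- That the planned 1.25 effect will be hidden. This depends on an unknown share.
- That the effect would be reversed. The lowest value in the second model, 0.99, is null. In the first model the ratio falls clearly below 1 only at an assumed 15% share (0.92), for which the article offers no basis.

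**What to change.** In the survival paragraph of Statistical Analysis, adopt one of two rules:
- Start unadjusted and quality-adjusted survival at the index time: ALI onset in the case and the same time since admission in the matched control. Use only controls alive and ALI-free at that time.
- Keep admission as time zero and treat ALI as a time-dependent covariate.

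State that the time-at-risk matching described for exposures also governs the burden comparison, and align the Abstract and the section on attributable burden with it. Requiring the control to be still in hospital at the index time is optional; it is not needed to remove the immortal time.

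The cost of the first rule is one derived date per pair, which the exposure window already requires, and replacement of a few candidate controls who die early. If they are dropped without replacement, power in the simulation is about 77% to 79% for shares up to 5% and 73% at 10%. The index-time estimate applies to patients who survive to that time, and the report should say so.
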